### 8.4. Study stopping criteria

Throughout the study period, if any SAE or serious complain happens, PI is obligated to review subject's data immediately and make medical judgment if the SAE is vaccine-related or not. If any of the following situations occurs, PI must inform the DSMB and NHRI/CRO and study recruitment should be suspended until further notice.

- (1) Any subject with severe local reaction, including ulceration, abscess or necrosis.
- (2) Any subject develops laryngospasm, bronchospasm or anaphylaxis.
- (3) Two of more subjects develop severe urticaria.
- (4) Any vaccine-related SAE during study period.

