All subjects should complete at least 7 visits, including the last 2 telephone visits. Additional visit, Visit 2a (Day 3) and Visit 4a (Day 24) will be conducted first in Part I for monitoring creatine kinase (CPK) in subjects at the third day after 1st and 2nd vaccination. Whether these 2 visits will be performed again in Part II depended on the DSMB's professional judgments. The immune response, including serum IgG and neutralizing antibody titers, will be assessed at Visit 2, 4 and 5 (baseline, Day 21 and Day 42), and immune epitope mapping of EV71vac will be conducted at Visit 2 and Visit 5. A post-vaccination diary card will be dispensed for the solicited/unsolicited symptoms, and a telephone follow-up will be conducted 7 days after each vaccination and/or 14 days after second vaccination (only for subjects in Block C). The safety of EV71 vaccine will be monitored throughout the whole study period.

The investigator team (Principal Investigator and Co-Investigators) should, on an ongoing basis, review the subject's safety data (including all AE recorded on the diary card and detected during study period) immediately and make medical judgment whether the adverse event is vaccine-related or not. The independent DSMB should monitor all the safety data as well. The second part of study could be conducted only when there is no safety concerns regarding the EV71 vaccine (evaluated on 14 days after the second vaccination of Block C). Moreover, the study recruitment should be suspended if any of the following criteria is met.

- (1) Any subject with severe local reaction, including ulceration, abscess or necrosis.
- (2) Any subject develops laryngospasm, bronchospasm or anaphylaxis.
- (3) Two or more subjects develop severe urticaria.
- (4) Any vaccine-related SAE during study period.

All subjects will be asked to preserve the residue blood samples for further research through a separate question in informed consent.

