**Figure 3-1 Study subject enrollment process:**

[figure not shown]

The study recruitment should be carried out in 2 parts, Part I and Part II.

**Part I:** This part of study will be conducted in one center. It will consist of the first 10 subjects who will have sequential enrollment. Following a blocking factor of safety, these subjects will be recruited in 3 blocks, Block A, Block B and Block C.

- ◆ **Block A:** Only the first subject will be assigned to Block A. He/she will be vaccinated with EV 71 vaccine 0.25 ml (5 µg total protein with adjuvant 150 µg AlPO4).
- ◆ **Block B:** Block B will be initiated 7 days safety monitoring after the first vaccination of Block A. There will be 2 subjects recruited into this block at the same time, and they will be randomized into two dosing groups, Group A05 and Group B10, respectively.
- ◆ **Block C:** Block C will be initiated 7 days safety monitoring after the second vaccination of Block B and 7 subjects will be enrolled into this block at the same time. Three of them will be randomly assigned to Group A05 and the other 4 subjects will be randomly assigned to Group B10.

The investigator team (Principal Investigator and Co-Investigators) should, on an ongoing basis, review the subject's safety data, including all solicited/unsolicited symptoms recorded on the diary card and all AE detected during study period, immediately and make medical judgment whether the adverse event is vaccine-related or not. Block B and Block C will only be taken place after the investigator confirms the initial safety of prior block.

**Part II:** This part of study will be conducted in two centers. It will consist of the rest 50 subjects and should be initiated after the DSMB (Data and Safety Monitoring Board) evaluation conducted 14 days after the second vaccination of Block C. Subjects in this part will be randomized equally to Group A05 and Group B10.

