#### **4.3.2. Contraindications to second vaccination**

The following conditions constitute a contraindication to vaccination and those should be

checked prior to second vaccination (at Visit 3 and Visit 4):

(1) Subject with any abnormal laboratory results\* at safety screening visit (Visit 3):

\* Subject with ALT/AST or creatinine  $> 1 \times \text{ULN}$  but  $< 2.5 \times \text{ULN}$  could be re-tested 1 week later.

(2) Pregnancy

(3) Subject with fever defined as oral temperature  $\geq 37.5^{\circ}\text{C}$  at the time before second vaccination.

(4) Subject with acute disease at the time before the second vaccination (defined as the presence of a moderate or severe illness\*\* with or without fever).

\*\* All vaccines can be administered to persons with a minor illness such as diarrhea, mild upper respiratory infection with low-grade febrile illness, i.e. oral temperature  $< 37.5^{\circ}\text{C}$ .

Once a subject meets any of the contraindication, the second vaccination can be administrated at the later day, within a 3-day delay (Day 21 to Day 24), or be withdrawn at investigator's discretion. The investigator should document on the Vaccination page of the CRF, the possible reasons for delay administration/withdrawal (AE, SAE or other) and whether the decision to discontinue further vaccination was made by the subject or the investigator.

Any subject who receive the vaccination with dosage deviation or who does not receive the second vaccination on schedule may not necessarily be withdrawn from the study as further study procedures and the follow-up visits may be performed.

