### **8.3.2. DSMB process**

The study could be initiated only after an independent DSMB has reviewed the relevant study materials. 14 days after the last subject of Part 1 has received the second vaccination dose, DSMB will review the initial safety data for each of these 10 study subjects. If no SAE happens prior to interim analysis, the DSMB will recommend continuation of the study recruitment for Part 2.

Throughout the study period in either Part 1 or Part 2, if any vaccine related SAE or serious complaints happen, the PI has to inform DSMB about the event. The DSMB is to make a decision on whether the SAE meets the stopping criteria of the study (see [Section 8.4](#)) and conclude if further enrollment of the subjects in the study should be continued or suspended, and will inform the NHRI and PI accordingly. The PI is to inform the NHRI about the study status at the same time. The sponsor is responsible to make the final decision about further enrollment and continuation of the study.

An emergency DSMB meeting can happen any time during the study period.

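### A met stopping criterion suspends recruitment only, so second injections already pending are not automatically held while the DSMB reviews the event

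*Protocol*

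**What the plan says.** Section 8.4 names four events: a severe local reaction, laryngospasm/bronchospasm/anaphylaxis, severe urticaria in two or more subjects, and any vaccine-related SAE. If any occurs, "PI must inform the DSMB and NHRI/CRO and study recruitment should be suspended until further notice". Part VIII of the synopsis lists the same events under the instruction "Moreover, the study recruitment should be suspended if any of the following criteria is met".

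Section 8.3.2 has the DSMB decide whether a reported SAE meets the criteria and "conclude if further enrollment of the subjects in the study should be continued or suspended". The sponsor then takes the final decision on enrolment and on continuing the study. On timing, the section says only "An emergency DSMB meeting can happen any time during the study period".

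Every subject receives two injections, on Day 0 and on Day 21 with up to 3 days' delay. The contraindications to the second one (Section 4.3.2) are the subject's own laboratory results, pregnancy, fever and acute illness. The response to a contraindication is that "the second vaccination can be administrated at the later day, within a 3-day delay (Day 21 to Day 24", or withdrawal at the investigator's discretion.

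**The concern.** Suspending recruitment is not the same as suspending vaccination. In a two-dose schedule, each subject who has had the first injection waits three weeks for another injection of the same product. This is a Phase I study whose protocol reports only preclinical experience with the vaccine. An anaphylaxis or a vaccine-related SAE after a first dose is therefore a warning for those subjects at least as much as for people not yet enrolled. The automatic rule covers only the second group. For the first, the next injection goes ahead unless someone intervenes before it is due.

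**Working it through.** No plan figure has to be reproduced; Section 10.6 gives no sample-size calculation. The check compares the sections and counts pending doses.

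**Inputs.** Block sizes (Section 3.1, Table 6-1): A = 1 (A05); B = 2 (1 A05, 1 B10); C = 7 (3 A05, 4 B10); Part II = 50. Gates: Block B starts 7 days after Block A's first dose, Block C starts 7 days after Block B's second dose, and Part II starts after the DSMB evaluation 14 days after Block C's second dose. Second dose: Day 21 to 24.

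**Earliest timeline, with Block A's first dose as study day 0.**
- Block B first dose: from day 7.
- Block A second dose: days 21 to 24.
- Block B second dose: from day 7 + 21 = 28.
- Block C first dose: from day 28 + 7 = 35, after all second doses in Blocks A and B are due.

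**Second doses pending when a criterion is met after a first dose.**

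| Period | Pending | In other subjects (one affected) |
|---|---|---|
| Block A alone, days 0 to 7 | 1 | 1 − 1 = 0 |
| Blocks A and B overlapping | up to 1 + 2 = 3 | up to 3 − 1 = 2 |
| Block C between doses | 3 + 4 = 7 | 7 − 1 = 6 |
| Part II | 1 to 50, by accrual | 0 to 49 |

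The urticaria criterion needs two affected subjects, so for Block C the last column becomes 7 − 2 = 5.

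**Part II under assumed accrual.** The protocol gives no rate. With steady accrual and a 21-day gap, about three weeks of accrual are pending at any time: 3 × 5 = 15 at 5 per week, 3 × 10 = 30 at 10 per week, and all 50 at about 50/3 ≈ 17 per week or faster. Once the 60th subject is enrolled, suspending recruitment stops nothing, although second doses remain due for up to 24 days.

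**What the suspension does between doses.** Block C is filled at once: "7 subjects will be enrolled into this block at the same time". Part II is already closed until the DSMB evaluation. Between Block C's doses no recruitment is due, so the suspension withholds none of the 7 injections. The same holds for Block B's own doses, because Block C is already gated: "Block B and Block C will only be taken place after the investigator confirms the initial safety of prior block". The rule does protect those still to be enrolled; after a Block C event that is 50 subjects, or 50 × 2 = 100 injections.

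**Other clauses that could hold a second dose.**
- Section 4.3.2: no item refers to a stopping event, in the subject or in anyone else. The illness item would catch an event still present as moderate or severe illness at Visit 4, but the response may be only a delay to Day 24. A resolved anaphylaxis is not listed.
- Section 4.3.1, item (4): withdrawal on the physician's view of that subject's own interest.
- Sections 3.3 and 18: the study may be suspended or discontinued; both are discretionary.
- Section 8.3.1: the DSMB may recommend continuation, termination or modification; this is advisory.
- Section 8.3.5: a recommendation to stop, by majority vote, after review.

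None acts automatically before the DSMB has met.

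**The case against.** The strongest reply is that the protocol has more safeguards than Section 8.4 alone suggests. Section 8.3.5 links the DSMB's stop recommendation directly to the stopping criteria, and that recommendation concerns the study, not only recruitment. Section 8.3.1 already lets the DSMB recommend modifications. Withdrawal criteria are checked at Visit 3 and again before vaccination at Visit 4, so each second injection passes two scheduled checks. The investigator must review an SAE at once, and the study can be suspended at any time. A competent team would probably pause dosing. For an event after all second doses have been given, the gap is nil.

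Much of this is right, and it narrows the gap to the time between the event and a decision by the DSMB, the sponsor or the investigator. It does not close it. The DSMB vote has no deadline before the next injection. The pre-dose checks rest on judgment, mainly of the individual's own condition, and so do little for a healthy subject awaiting the same vaccine. Pre-set stopping criteria exist so that the first response does not depend on discretion.

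**Conclusion.** The concern holds. Section 8.4 and the synopsis attach one automatic restriction on exposure to a stopping event, and it does not reach subjects between doses. In Part I, up to 3 pending second injections (Blocks A and B) or 7 (Block C) are not automatically held; with one affected subject, up to 2 or 6 of them belong to others. The overlap count of 3 assumes that Block B starts before Block A's second dose. The Part II figure cannot be fixed without an accrual rate.

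The protocol permits a dosing pause but does not require one. This should be corrected. It is a safety rule governing conduct and affects no planned analysis.

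**What to change.** Amend Section 8.4 and the synopsis so that a met criterion suspends recruitment and all further vaccination, including pending second doses of enrolled subjects, until the DSMB has reviewed the event. Reword Section 8.3.2 so that the DSMB concludes on both enrolment and dosing. Add to Section 4.3.2 that a subject who has had a stopping event does not receive the second dose, as an exclusion and not as a delay to Day 24.

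Two additions would be useful: a time limit for the DSMB review, and a rule for subjects whose Day 21 to 24 window passes during the hold.

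The cost is a wording amendment in four places, which needs IRB approval because it bears on subject risk (Section 17). Some second injections may be late or omitted. Visit 5 is timed from the first dose (Table 5-2), so a late second dose shortens the interval before the Day 42 sample. Those subjects can remain in follow-up: Section 4.3.2 already provides that a subject who "does not receive the second vaccination on schedule may not necessarily be withdrawn from the study".

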## 9. Study Endpoints

### 9.1. Primary endpoint

- ◆ The percentage, intensity and relationship to vaccination of local and systemic signs and symptoms at a 5- $\mu$ g and 10- $\mu$ g dose under the following time frames:
  - Solicited adverse events: during 7-day follow-up period
  - Unsolicited adverse events: during 21-day follow-up period
- ◆ The occurrence of overall adverse events and serious adverse event at a 5- $\mu$ g and 10- $\mu$ g dose during the entire study period.

### 9.2. Secondary endpoints

- (1) Observed variables from baseline at a 5- $\mu$ g and 10- $\mu$ g dose on Day 21 and 42:
  - Serum IgG titers
  - Serum neutralizing antibody titers

- Epitope mapping (only on Day 42)
- (2) The change in the laboratory results:
  - Hematology
  - Biochemistry

## **10. Statistics**

### **10.1. Study cohorts to be evaluated**

#### **10.1.1. Total Vaccinated cohort (TVC)**

The Total Vaccinated cohort includes all vaccinated subjects who received at least one dose of study medication. For the total analysis of safety, this will include all vaccinated subjects for whom safety data are available. For the total analysis of immunogenicity, this will include vaccinated subjects for whom data concerning immunogenicity endpoint measures are available.

#### **10.1.2. According-To-Protocol (ATP) cohort for analysis of immunogenicity**

The ATP cohort for analysis of immunogenicity will include all vaccinated subjects and exclude below subjects:

- (1) Subjects are violating major protocol criteria.
- (2) Subjects do not have baseline or at least one post-baseline immunogenicity endpoint measures.

#### **10.1.3. According-To-Protocol (ATP) cohort for analysis of safety**

The ATP cohort for analysis of safety will include all vaccinated subjects and exclude below subjects:

- (1) Subjects are violating major protocol criteria.
- (2) Subjects who receive a vaccine not specified or forbidden in the protocol

### **10.2. Baseline and demographic characteristics**

Summary statistics will be provided for demographics (including age, gender, etc.) and for baseline characteristics (including physical examination, vital signs, and laboratory variables). The demographics and baseline characteristics will be presented as counts and percents for the qualitative variables or mean, SD, Min, Max., and range for the quantitative variables as appropriate.

### **10.3. Analysis of the primary objectives**

The primary objective is to evaluate the safety and reactogenicity of the EV71 vaccine at a 5-µg and 10-µg dose.

### 10.3.1. Variables

The primary endpoints include:

- (1) The percentage, intensity and relationship to vaccination of local and systemic signs and symptoms at a 5- $\mu$ g and 10- $\mu$ g dose under the following time frames:
  - Solicited adverse events: during 7-day follow-up period
  - Unsolicited adverse events: during 21-day follow-up period
- (2) The occurrence of overall adverse events and serious adverse event at a 5- $\mu$ g and 10- $\mu$ g dose during the entire study period.

### 10.3.2. Statistical hypothesis, model, and method of analysis

No specific hypothesis is planned to be performed. The main objective is to assess the incidence rate of adverse events. All results will be presented using descriptive statistics.

All solicited and unsolicited adverse events during the study period will be record and analyzed. Adverse events will be coded with MedDRA coding system and will be summarized by system of organ and preferred term. The percentage of subjects with adverse event (solicited and unsolicited) will be tabulated with count, percentage and 95% confidence Interval for each vaccine dose and overall results. The severity and relationship to study medication of adverse events will be summarized as well.

The incidence of serious adverse events will also be summarized; furthermore, the brief summary about serious adverse event will be presented.

## 10.4. Analysis of secondary objectives

The secondary objectives include:

- (1) To evaluate the immunogenicity in terms of IgG titers induced by the EV71 vaccine at a 5- $\mu$ g and 10- $\mu$ g dose.
- (2) To evaluate the immunogenicity in terms of neutralizing antibody titers from baseline induced by the EV71 vaccine at a 5- $\mu$ g and 10- $\mu$ g dose.
- (3) To identify the immunodominant epitopes of EV71 virus by human serum.

### 10.4.1. Variables

The secondary endpoints include:

- (1) Observed variables from baseline at a 5- $\mu$ g and 10- $\mu$ g dose on Day 21 and 42:
  - Serum IgG titers
  - Serum neutralizing antibody titers
  - Epitope mapping (only on Day 42)

The immunogenicity parameters include serum IgG titers and neutralizing antibody titers on baseline, Day 21 and Day 42, and immune epitope mapping of EV71vac will be conducted on baseline and Day 42.

The serum IgG and neutralizing antibody titers on baseline, Day 21 and Day 42 will be summarized descriptively and the change from baseline will be tested by paired T-test or

Wilcoxon signed rank test under significance level 0.05. The results of immune epitope mapping will be summarized descriptively as well.

(2) The change in the laboratory results:

- Hematology
- Biochemistry

The analysis of laboratory includes hematology and biochemistry.

Hematology tests include CBC, such as Hb, Hct, RBC count, WBC count, WBC differential and platelet count; and biochemistry tests include ALT, AST,  $\gamma$ GT, alkaline phosphatase, total bilirubin, total protein, albumin, CPK, BUN, creatinine, uric acid, total cholesterol, triglyceride and glucose (fasting).

The descriptive summary results of laboratory for the baseline, each study visit, end of visit, the change from baseline to end of visit will be presented and paired T-test or Wilcoxon signed rank test will be used to test change from baseline under significance level 0.05.

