| Distribution                            |                | X                              |                   |                     | X                              |                   |                  |                      |                                 |
| Return                                  |                |                                |                   |                     | X                              |                   | X                |                      |                                 |
| Concomitant medications                 | X              | X                              |                   | X                   | X                              |                   | X                | X *       | X *                  |
| Adverse events                          |                | X                              |                   | X                   | X                              |                   | X                | X *       | X *                  |
| Study completion                        |                |                                |                   |                     |                                |                   |                  |                      | X *                  |

 Body height will be only measured at Visit 1.

 Pregnancy test will be only conducted in female subject of childbearing potential.

 Hematology tests include CBC, such as Hb, Hct, RBC count, WBC count, WBC differential and platelet count.

 Biochemistry tests include ALT, AST, γGT, alkaline phosphatase, total bilirubin, total protein, albumin, BUN, creatinine, uric acid, total cholesterol, triglyceride and glucose (fasting).

† These procedures should be conducted before vaccination.

\* These study procedures will be conducted through telephone contact. \*\* For subjects in Block C, a 14-day telephone follow-up will also be taken place. ^ Creatine kinase (CPK) assay at Visit 2a and Visit 4a in Part I should be monitored at the 3rd days after each vaccination, the results should be evaluated by DSMB to decide if CPK should be monitored in Part II.

# ET: early termination (The final telephone follow-up may be omitted if a subject is withdrawn as a reason other than safety.)

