### 5.1. Visit 1 (Day -7~0) – Screening

At Visit 1, informed consent must be obtained prior to performing any procedures related to the study and after the healthy volunteer has received sufficient information about the study, the opportunity to ask any questions, and consider the options.

Subjects who have been screened should be listed on the Screening Log. Moreover, all screening procedures conducted and the primary reason for not continuing must be documented in the CRF, but no data will be entered into the database for all screened subjects who do not meet criteria for entering the study. No CRF other than the screening part should be completed for these subjects. The following study procedures will be conducted for screening assessments.

- (1) Record date of informed consent signed. Document in the subject's medical chart that he/she is participating in this study, informed consent has been obtained and a copy of the consent has been given to the subject.
- (2) Check inclusion/exclusion criteria.
- (3) Collect the demographic data, including date of birth, age, gender and ethnicity.
- (4) Collect relevant medical history and concurrent diseases. Where possible, diagnoses and not symptoms should be recorded.
- (5) Conduct a complete physical examination including the measurement of weight and height. Measure and record the oral temperature.

- (6) Collect urine samples for pregnancy test (in females of childbearing potential only).
- (7) Collect approximately 8 ml of whole blood sample for following local laboratory tests.
  - Hematological tests: CBC, including Hb, Hct, RBC count, WBC count, WBC differential and platelet count.
  - Biochemistry tests: ALT, AST,  $\gamma$ GT, alkaline phosphatase, total bilirubin, total protein, albumin, BUN, creatinine, uric acid, total cholesterol, triglyceride and glucose (fasting).
- (8) Review prior and concomitant medications. All medications, including vaccine(s), taken during the 30-day period before vaccination should be recorded.

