### 5.3. Visit 2a (Day 3± 1) – CPK Monitoring

Creatine kinase (CPK) monitoring will be performed in 10 subjects in Part I for 1st vaccination on Day 3 with an allowed a time window of 1 day. Whole blood sample for CPK test will be collected and analyzed by local laboratory.

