## 7.3. Safety

### 7.3.1. Physical examination / body temperature

Complete physical examinations and oral temperature determination should be conducted by investigator at screening, Visit 2 and 4 prior to vaccination, and the last return visit (Visit 5). A complete physical will include the examination of general appearance, HEENT (head, ears, eyes, nose, throat), neck (including thyroid), lymph nodes, skin, cardiovascular, pulmonary, abdomen, neurological system and musculoskeletal/joints.

For two vaccination visits (Visit 2 and Visit 4), body temperature should be measured prior to vaccine administration. Subject with fever defined as oral temperature  $\geq 37.5^{\circ}\text{C}$  should not receive study vaccine.

Body weight will be measured in indoor clothing, but without shoes at all visits, but body height will be measured only at screening visit. Body mass index (BMI) will be calculated by taking a subject's weight in kilograms (kg) and dividing by their height in meter squared ( $\text{m}^2$ ). A subject with BMI  $> 35$  at screening should be excluded from this study.

It must be recorded when any abnormality has been found out.

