### **7.3.3. Selected laboratory safety tests**

Fasting blood samples will be collected for hematological and biochemistry examinations at Visit 1, Visit 3 and Visit 5. These tests will be conducted by local laboratory in each center.

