#### **10.4.2. Safety**

The evaluated variables for safety include vital signs and physical examination.

(1) Vital signs

The summary of vital signs includes systolic/diastolic blood pressure, heart rate and body temperature. The descriptive summary results for the baseline, each study visit, and end of visit, the change from baseline to end of visit will be presented, and paired T-test or Wilcoxon signed rank test will be used to test change from baseline under significance level 0.05.

(2) Physical examination

The physical examination will be summarized descriptively by visit. Besides, the transition state of physical examination from baseline to end of visit will be summarized as well.

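### Section 10.4 plans change-from-baseline analyses of CPK, blood pressure and heart rate, but the protocol schedules no pre-vaccination CPK sample and no blood pressure or heart rate measurement

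*Protocol*

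**What the plan says.** **What is to be analysed.** Protocol section 10.4.1 lists the biochemistry tests as including "total bilirubin, total protein, albumin, CPK, BUN, creatinine, uric acid, total cholesterol, triglyceride and glucose (fasting". It promises summaries at baseline, at each visit and at the end, the change between the two, and a paired t-test or signed-rank test: "Wilcoxon signed rank test will be used to test change from baseline under significance level 0.05". Change in laboratory results is a secondary endpoint (9.2). Section 10.4.2 states: "The summary of vital signs includes systolic/diastolic blood pressure, heart rate and body temperature", with the same paired testing. Section 10.2 names vital signs among the baseline characteristics.

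**What is to be collected.** Section 7.3.3 fixes the timing of the safety bloods: "Fasting blood samples will be collected for hematological and biochemistry examinations at Visit 1, Visit 3 and Visit 5". Footnote 4 of Table 5-1 writes out the panel: "total bilirubin, total protein, albumin, BUN, creatinine, uric acid, total cholesterol, triglyceride and glucose (fasting". The Visit 1 list in 5.1 agrees, and the texts for Visits 3 and 5 refer back to it. CPK has its own visits: "Creatine kinase (CPK) monitoring will be performed in 10 subjects in Part I" at Visit 2a after dose 1, and correspondingly at Visit 4a after dose 2. The DSMB decides whether these visits are repeated in Part II. For physical measurements, 7.3.1 states: "Complete physical examinations and oral temperature determination should be conducted by investigator at screening". It adds weight and height and lists the body systems to be examined.

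**The concern.** The analysis section names variables for which the data collection sections provide no baseline, or no measurement at all. A later statistical analysis plan can refine an analysis, but it cannot supply a sample that was never scheduled.

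The CPK gap carries more weight. CPK is singled out for two extra visits, and the DSMB must use the results to decide whether the monitoring continues in Part II. The trial has no control arm, so a subject's own pre-dose value would be the natural reference for a raised Day 3 result. Screening does not supply one, because CPK is not in the screening panel. Once the first dose has been given, an unvaccinated value cannot be recovered, and section 10.5 applies no method for missing data.

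The blood pressure and heart rate gap is a mismatch between the analysis text and the schedule. These variables do not appear among the endpoints in section 9.

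**Working it through.** The protocol gives no figure to reproduce here (10.6 treats sample size as not applicable). The check compares what is analysed with what is collected, then counts.

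**1. Analyte lists.**
- Collected (Table 5-1 footnote 4; 5.1; 7.3.3.2): ALT, AST, γGT, alkaline phosphatase, total bilirubin, total protein, albumin, BUN, creatinine, uric acid, total cholesterol, triglyceride, glucose = 13.
- Analysed (10.4.1): the same 13 plus CPK = 14.
- Difference: 14 − 13 = 1, which is CPK.

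**2. CPK by visit.**

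| Visit | Blood scheduled | CPK? |
|---|---|---|
| 1 (screening) | 13-analyte panel, haematology | No |
| 2 (before dose 1) | Immunogenicity only | No |
| 2a (Day 3±1) | CPK, Part I | Yes, after dose 1 |
| 3 (Day 14+3) | Same panel as screening | No |
| 4 (before dose 2) | Immunogenicity only | No |
| 4a (Day 24) | CPK, Part I | Yes, intended after dose 2 |
| 5 (Day 42±3) | Same panel as screening | No |

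The Visit 4a window is 24+3 days in Tables 5-1 and 5-2 but ±3 in section 5.6. The wider version reaches back to Day 24 − 3 = 21. Even then the sample follows dose 1, so it is not an unvaccinated baseline.

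**3. Pairs available for CPK.** Part I plans 10 subjects × 2 samples = 20 CPK values. Scheduled pre-vaccination values: 0. Scheduled Visit 5 values: 0. Pairs for change from baseline: 0 of 10. If the DSMB extends the monitoring unchanged, 50 × 2 = 100 further values would also lack a baseline.

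**4. Vital signs.** Section 10.4.2 names four: systolic pressure, diastolic pressure, heart rate and body temperature. Table 5-1, the visit lists in section 5 and section 7.3.1 provide for oral temperature only. Three of the four have no scheduled measurement.

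**5. What a pre-dose sample in Part I would allow.** From Table 6-1, A05 has 1 + 1 + 3 = 5 subjects and B10 has 0 + 1 + 4 = 5. The smallest attainable two-sided exact signed-rank p-value with n pairs is 2 × (1/2)^n:
- n = 5 (one dose group): 2 × (1/2)^5 = 0.0625
- n = 10 (pooled): 2 × (1/2)^10 = 0.00195

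Within a dose group this test cannot reach 0.05 even if all five subjects change in the same direction. The paired t-test has no such floor, but it then relies on normality of five differences, which five values cannot check.

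**The case against.** Listing CPK under biochemistry is not itself an error. Table 5-1 marks CPK in the biochemistry row at Visits 2a and 4a, and 10.4.1 also promises summaries by visit, which can be produced. Only the change from baseline fails. This stands, and the point is limited to it.

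A reader might go further and infer three things that the documents do not support:

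- **That blood pressure and heart rate are never measured.** A complete examination that includes the cardiovascular system may well involve both, 10.2 expects baseline vital signs, and the CRF is not shown. What can be said is that no schedule row, visit list or assessment section names them or provides for recording them.
- **That the CPK values are unusable.** They can be compared with the normal range, and the investigator's causality assessment (Table 7-4) weighs other explanations. A baseline would improve interpretation; without one, some interpretation remains.
- **That the decision to open Part II is compromised.** The CPK decision concerns only whether Visits 2a and 4a are repeated. Opening Part II rests on the safety data as a whole (3.3, 8.3.2), and nothing says that the CPK decision uses change from baseline.

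It is also fair to object that adding CPK to the existing panels is more than one extra assay. Section 4.2.2 item 8 excludes subjects with an abnormal screening laboratory result, and 4.3.2 makes an abnormal Visit 3 result a contraindication to the second dose, with a re-test provision naming only ALT/AST and creatinine. Section 7.3.3.2 words both rules in terms of significant abnormalities. As written, CPK could fall under these rules. That has to be settled along with the addition, but it does not remove the inconsistency.

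**Conclusion.** The inconsistency is confirmed. The planned change-from-baseline analysis of CPK has 0 pairs, since neither a pre-dose nor a Visit 5 value is scheduled. The planned analyses of systolic pressure, diastolic pressure and heart rate rest on measurements that the protocol does not schedule. This assumes that the written schedule is the full list of what is collected; a CRF page recording blood pressure and pulse would narrow the second part to a missing cross-reference.

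The severity is moderate. The primary endpoint is adverse events, no hypothesis is planned for it, and no stopping criterion in 8.4 refers to these variables. The CPK part deserves action before the first subject is dosed, because the missing value cannot be obtained afterwards. The vital-signs part could be closed by an edit.

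**What to change.** **CPK.** Choose one:
- Run CPK on the roughly 8 ml of safety blood already drawn at Visit 1, and again at Visit 3, at least in Part I, and in Part II if the monitoring continues. Label Visit 3 as the reference before dose 2; it follows dose 1 and is not an unvaccinated baseline. Report the change descriptively, by dose group and pooled, without a test at 0.05 within dose group. Replace the change to the end visit with the change to Visits 2a and 4a, since no Visit 5 CPK is planned.
- Otherwise, remove CPK from the change-from-baseline analysis in 10.4.1 and state that it will be summarised by visit and against the normal range.

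If CPK is added, the sponsor must reconcile this with 4.2.2 item 8, 4.3.2 and 7.3.3, and state whether the rules on abnormal laboratory results cover CPK. Reconcile the two Visit 4a windows in the same amendment.

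**Blood pressure and heart rate.** Either add them to Table 5-1, the visit lists and 7.3.1 at the existing physical examinations, with a CRF field, or delete them from 10.4.2 and limit the vital signs in 10.2 to temperature.

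**Cost.** One more assay on samples already taken and a routine vital-signs line, plus the wording on the laboratory rules; or, for the deletion route, edits to 10.2, 10.4.1 and 10.4.2. No sample size or power figure changes.
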